## Abstract

Background: Hwa-Byung is a culturally bound syndrome prevalent in Korea, characterized by intense emotional distress and physical symptoms related to suppressed anger. Patients frequently report experiencing chest tightness, heat sensations, and globus pharyngeus (the sensation of a lump in the throat). These physical symptoms often accompany psychological distress and can exacerbate the sense of frustration and helplessness associated with the condition. The distinctive presentation of these symptoms highlights the necessity for therapeutic interventions that address both the emotional and physical aspects of Hwa-Byung. Conventional therapeutic methods, such as Emotion-to-Emotion Therapy (ETE), have shown efficacy in treating this condition. This study aims to assess the efficacy of Virtual Reality-based Emotion-to-Emotion Therapy (VR-based ETE) compared to conventional ETE, utilizing immersive digital platforms to enhance therapeutic engagement. Methods: This single-center, randomized, assessor-blind, parallel-group clinical trial will enroll 96 participants, evenly divided into two experimental groups and one control group. Over eight weeks, each participant will undergo 12 intervention sessions. Experimental group 1 will receive conventional ETE, experimental group 2 will receive VR-based ETE, and the control group will receive Hwa-Byung management training materials. The primary outcome will be the change in symptoms, measured by the Likert Scale for Major Symptoms of Hwa-Byung from baseline to 8 weeks. Secondary outcomes will include psychometric scales and physiological measures such as the core seven-emotions inventory short form, physical health questionnaire, stress response index, Beck depression inventory, state-trait anger expression inventory, state-trait anxiety inventory, functional near-infrared spectroscopy, and heart rate variability. For economic efficiency assessment, quality-adjusted life-years will be the primary outcome using the EuroQol-5 dimension, and the secondary outcome will be using the EuroQol visual analog scale. Discussion: ETE is a recognized oriental psychotherapy that enhances symptom management, self-regulation, and stress coping. VR is expected to deepen treatment immersion. By combining these strengths, VR-ETE may further improve emotion regulation and alleviate psychosomatic symptoms. If successful, this study will not only advance the treatment of Hwa-Byung but also contribute to the modernization of traditional Korean medicine through the integration of digital therapies.

## 1. Introduction

Emotion dysregulation is a key factor in many psychosomatic and psychiatric disorders globally [1]. For example, anxiety disorders often involve excessive, uncontrollable worry and fear; depression is marked by intense sadness, irritability, and frustration that are hard to regulate; and anger disorders feature frequent, intense outbursts disproportionate to their triggers, indicating poor emotional control [2,3,4]. Emotion dysregulation can manifest in various forms, contributing to the overall symptomatology and impairment in each condition [5]. It contributes to the development of conditions like Hwa-Byung [6]. Hwa-Byung, also known as “anger syndrome”, is attributed to the suppression of anger within a Korean cultural context [7]. It affects approximately 4.1–13.3% of South Korea’s general population, with a higher prevalence among middle-aged women [8,9,10]. Patients frequently endure prolonged periods of anger, displaying symptoms such as chest discomfort, heat sensations, heartburn, globus pharyngeal, and frequent feelings of unfairness and resentment, which are major diagnostic criteria for Hwa-Byung [11,12]. The trajectory of Hwa-Byung typically progresses from prolonged psychological stress to physical symptoms such as chest tightness and heat sensations, reflecting a build-up of suppressed emotions over time [13]. Hwa-Byung is often rooted in sociocultural expectations in Korea, where expressing anger directly is sometimes discouraged, especially within familial and social settings [13]. Research indicates that the inability to express anger, lack of social support, spousal criticism, or interpersonal hypersensitivity increases the likelihood of developing Hwa-Byung [14]. Although Hwa-Byung is culturally specific to Korea, the underlying emotional dysregulation is universal and mirrors psychosomatic conditions seen globally, such as anxiety and depression [6]. Similar culturally specific syndromes, such as taijin kyofusho in Japan and ataque de nervios in Latin American populations, have been studied to understand the psychological and therapeutic approaches tailored to culturally bound expressions of distress [15]. These studies underscore the importance of a cultural lens in understanding psychological issues, as an individual’s history within their cultural context shapes symptom presentation and treatment outcomes, highlighting the need for culturally adaptive interventions [13,15].

Emotion-to-Emotion Therapy (ETE) is a psychotherapy based on the theory of the five elements, the basic principle of traditional Korean medicine, which treats mental and physical ailments by alleviating pathological emotions and is recommended in clinical practice guidelines for the treatment of Hwa-Byung [16]. The five emotions of anger, joy, thought, sadness and melancholy, fear and surprise are assigned to each of the five elements: Tree, Fire, Earth, Metal, and Water, dynamically influencing each other [17]. The treatment is based on controlling this dynamic relationship, analyzing the patient’s emotions and feelings, and using the corresponding emotions and feelings in the Five Elements to help the patient achieve a stable state [17]. Traditional Korean medicine psychotherapy employs a holistic approach aimed at balancing physical and emotional states through methods such as meditation and mind–body exercises [18]. ETE applies these principles to address the psychosomatic symptoms of Hwa-Byung by helping patients identify and regulate core emotions, such as anger, resentment, and sorrow, thus restoring emotional balance [12]. This therapy also promotes self-compassion and compassion toward others, facilitating the transition from emotional distress to resilience and enabling patients to manage anger, adapt to stress, and resume healthy functioning [13].

Virtual Reality (VR) therapy has been demonstrated to be an efficacious treatment for a range of mental health disorders, alleviating patients’ stress [19,20]. The COVID-19 pandemic has led to an increase in in-person interactions in all areas of life with these interactions becoming increasingly crucial in the field of psychotherapy [21,22]. VR is well suited for non-face-to-face interaction and provides a guaranteed, reproducible, controllable, and safe environment for therapy and training [23,24].

There is evidence that VR can enhance psychological treatments for a variety of neuropsychiatric diseases, such as anxiety disorders [19,25,26]. However, there is a paucity of research investigating its potential for the treatment of Hwa-Byung. Thereby, the integration of Virtual Reality (VR) therapy into the treatment of Hwa-Byung represents a promising avenue for enabling patients to safely confront stressors and emotional triggers within a structured, therapeutic setting. A potential VR intervention design is illustrated in Figure 1. The proposed intervention design for Hwa-Byung treatment through VR comprises an initial assessment, immersive exposure to VR scenarios pertinent to emotional regulation, real-time biofeedback, and guided reflection sessions. These steps provide a structured approach for addressing the emotional and physiological symptoms of Hwa-Byung, thereby enhancing the therapeutic efficacy of VR.

Patients suffering from anger, depression, and anxiety associated with Hwa-Byung are prone to emotional instability, potentially leading to comorbid somatoform disorders. This vulnerability complicates their ability to manage daily tasks and interpersonal relationships, thereby increasing the frequency of medical treatments and associated costs [14]. Indeed, statistical data reveal that the number of Hwa-Byung cases treated in Korea increased by 10.5% from 2015 (12,592 patients) to 2019 (14,064 patients), with medical expenses rising by 48.2% over the same period [27]. Although Selective Serotonin Reuptake Inhibitors (SSRIs) have been employed to manage symptoms [28], comprehensive clinical studies are lacking. A retrospective study on the emotional characteristics of Hwa-Byung patients showed a dynamic change over time in emotions such as sorrow, underscoring the need for a therapy that considers these unique emotional traits [29]. Traditional Korean medicine psychotherapy addresses psychological conditions holistically, combining methods like herbal medicine, acupuncture, and emotional regulation techniques [30]. Despite some applications of traditional Korean medicine psychotherapy for Hwa-Byung [31], there is a lack of standardized protocols, especially those that address emotions per se. Therefore, further research is needed to confirm the efficacy of emotion-to-emotion therapy focused on specific emotions and to determine the most appropriate method of application for Hwa-Byung.

Quality-Adjusted Life-Year (QALY) is a widely used measure in healthcare cost-effectiveness analysis, combining quality and length of life to evaluate treatment value [32]. QALY assessments are commonly employed in countries like the UK and the US to guide resource allocation by balancing costs with patient benefits [33,34]. For VR-based therapies, QALY offers insights into cost effectiveness compared to traditional methods, showing that high QALY scores support the economic feasibility of innovative treatments like VR-based ETE, which may help reduce the long-term burden of conditions such as Hwa-Byung [35].

This study aims to determine the safety, effectiveness, and cost effectiveness of virtual reality-based emotion-to-emotion therapy compared to traditional emotion-to-emotion therapy for Hwa-Byung.

## 2. Methods/Design

### 2.1. Study Design

This study is a single center, randomized, assessor-blind, parallel-group clinical trial. This clinical trial will be conducted at Daejeon Korean Medicine Hospital of Daejeon University. This protocol (version 1.2, October 2022) complies with the Standard Protocol Recommendations for Interventional Trials (SPIRIT) guidelines [36]. The SPIRIT schedule of enrollment, interventions, and assessments is shown in Figure 2. The flowchart of this study is shown in Figure 3. This study was registered in the Clinical Research Information Service of the Republic of Korea (Trial Registration Number: KCT0007871, registered on 3 November 2022, available at [https://cris.nih.go.kr/cris/search/detailSearch.do/27510 (accessed on 25 May 2024)].

### 2.2. Study Procedure

Before conducting this clinical trial, the investigator will explain the “informed consent form” to the participants and receive written consent from the participants for the clinical trial based on their free will after ensuring that they have sufficiently understood what is required of them. The subjects will be given a screening code after obtaining their consent:

# DJ-S-ZZZ [DJ: Daejeon Korean Medicine Hospital of Daejeon University, S: initial screening, ZZZ: Serial number [001, 002~]] [ex. DJ-S-012: 12th applicant for screening of Daejeon Korean Medicine Hospital of Daejeon University].

The eligible subjects who meet the inclusion and exclusion criteria will be selected based on a demographic survey, vital signs (with systolic blood pressure, pulse rate, and body temperature falling within normal ranges), medical history (including chief complaint, onset, motif, past history, smoking, and alcohol ingestion to exclude candidates with cardiovascular disease, severe respiratory conditions, or significant mental health disorders unrelated to Hwa-Byung), chest X-ray, electrocardiography (EKG), laboratory tests, Beck Depression Inventory (BDI) (excluding subjects who score 2 or higher on item 9 to minimize suicide risk), and Hwa-Byung Diagnostic Interview Schedule (HBDIS) at screening. The included subjects will be assigned an identification code:

# DJ-E-ZZZ [DJ: Daejeon Korean Medicine Hospital of Daejeon University, E: initial enrollment, ZZZ: Serial number [001, 002~]] [ex. DJ-E-014: 14th registered subjects of Daejeon Korean Medicine Hospital of Daejeon University].

Screening tests should be conducted within ten days prior to visit 1 (baseline visit) and visit 13 should be conducted within 16 weeks (±7 days). At visit 1, the investigator will check the results of the screening test (including chest X-ray and laboratory tests), physical examination, and changes in medical history and concomitant medication between the screening and visit 1. The subjects will be randomly assigned to one of three groups: experimental group 1, experimental group 2, or the control group, and each subject will be provided with a unique identification code for tracking and analysis purposes. Before the intervention, subjects will complete the Likert Scale for Major Symptoms of Hwa-Byung (HB-M), The Core Seven-Emotions Inventory Short Form (CSEI-S), Patient Health Questionnaire-15 (PHQ-15), Stress Response Index (SRI), State-Trait Anxiety Inventory (STAI), State-Trait Anger Expression Inventory (STAXI), functional Near-Infrared Spectroscopy (fNIRS) (device name: NS1-H20AM), Heart Rate Variability (HRV), efficacy analysis (EQ-5D, EQ-VAS), and cost analysis. Experimental group 1 will be treated with ETE, and experimental group 2 will be treated with VR-based ETE, while the control group will receive Hwa-Byung management training materials only. At visits 1–12, the investigator will check for adverse effects and changes in medical history and concomitant drugs and patient compliance; subjects will receive ETE or VR-based ETE according to the corresponding intervention schedule at each visit. Tests and assessments will be conducted according to the following schedule: visit 8 (efficacy analysis; EQ-5D, EQ-VAS, cost analysis); visit 12 (HB-M, CSEI-S, PHQ-15, SRI, BDI, STAXI, STAI, fNIRS, HRV, efficacy assessment; EQ-5D, EQ-VAS, cost analysis, laboratory tests); and visit 13 (follow-up visit; HB-M, CSEI-S, PHQ-15, SRI, BDI, STAXI, STAI, efficacy assessment; EQ-5D, EQ-VAS, cost analysis, physical examination, adverse effects, changes in medical history and concomitant drugs).

Additional visits may be made at any time other than the scheduled visit when deemed necessary at the request of the subject or discretion of the researcher. If a subject visits on an unscheduled day, adverse reactions, concomitant medications, results of tests performed, and subsequent medical treatment must be recorded in the case record. Even in the case of subjects who drop out, laboratory tests, pregnancy diagnostic tests, and efficacy evaluation tests can be performed during additional visits.

### 2.3. Clinical Assessments

In this study, the clinical assessments are as follows: vital signs (blood pressure, pulse rate, body temperature); laboratory tests (complete blood cell count: hemoglobin, hematocrit, red blood cell count, white blood cell count, platelet count, erythrocyte sedimentation rate; blood chemistry test: total protein, albumin, aspartate transaminase, alanine transaminase, gamma-glutamyl transpeptidase, total bilirubin, blood urea nitrogen, creatinine, glucose, Na+, K+, Cl−, free thyroxine, thyroid-stimulating hormone; urine analysis: specific gravity, pH, erythrocyte, leukocyte, nitrite, protein, glucose, ketone, urobilinogen, bilirubin, microscopy); pregnancy test (urine human chorionic gonadotropin, only for fertile women to ensure that the results are negative, but for menstruation will be conducted in visit 1); EKG (12-lead electrocardiography); chest X-ray; HB-M; CSEI-S; PHQ-15; SRI; BDI; STAXI; STAI; fNIRS; HRV; EQ-5D; EQ-VAS; and cost analysis.

### 2.4. Study Populations

#### 2.4.1. Inclusion Criteria

(1)Aged 19 to 65 years;(2)Diagnosed with Hwa-Byung through HBDIS(3)Participants who voluntarily decided to participate and signed the consent form.

#### 2.4.2. Exclusion Criteria

(1)Participants with risk of suicide (scoring 2 or more points in BDI question 9, with specific suicidal thought or plan);(2)Participants with a history or present illness of severe psychiatric disorders (e.g., hallucination, delusion, etc., will be judged by a specialist in oriental neuropsychiatry or a resident who has been educated by a specialist in oriental neuropsychiatry and has clinical experience in neuropsychiatry of traditional Korean medicine for over 1 year) taking antipsychotic drugs to treat psychosis or receiving psychosis-related treatment;(3)Participants who have received Korean medical treatment or psychiatric treatment to improve symptoms of Hwa-Byung within the previous four weeks;(4)Seriously unstable medical conditions (the investigator will decide based on laboratory test, vital sign, etc.);(5)Participants with hyperthyroidism or hypothyroidism (over 1.5 times the upper reference limit or under 0.75 times the lower reference limit of TSH, Free T4, or taking medication due to hyperthyroidism or hypothyroidism);(6)Participants who are thought to be not appropriate to participate in this trial by the investigator.

#### 2.4.3. Sample Size

The statistical hypothesis test of the evaluation variable is two-sided, and the significance level will be set at 5%. The type 2 error (β) will be set to 0.2, and the power will be maintained at 80%. The ratio of the experimental 1, experimental 2, and control groups should be 1:1:1. We expect the HB-M reduction in the control group and experimental group to be 2.52 and 6.84, respectively, and pooled standard deviation 5.178 based on previous studies conducted with a design similar to this study [37]. Therefore, the required sample size for each group is expected to be “2 × 6.9^2^ × (1.96 + 0.84)^2^/(7.8 − 2.8)2 ≃ 30/group ”. In addition, considering a dropout rate of 25%, we decided to register 32 participants per group, for a total of 96 participants.

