## 3. Discussion

Hwa-Byung causes physical, social, and emotional stress not only to the patient but also to the family members who care for them [6]. Significant correlations exist between depression in wives and depression in husbands, adding a burden to family dynamics [48]. Additionally, patients often perceive their symptoms as persisting, even after apparent relief [49]. Therefore, to prevent stress from developing into a disease, it is necessary to manage stress in the daily environment using mind–body intervention techniques.

The extant research demonstrates that VR therapy provides effective symptom relief across varying time frames, thereby highlighting its potential for a lasting impact on emotional regulation disorders [50]. In the short term, VR therapy has been demonstrated to rapidly alleviate symptoms, with significant improvements achieved within just a few sessions for conditions such as anxiety with specific phobia [51]. These benefits frequently extend into the medium term, with studies indicating that emotional resilience can be sustained for up to four weeks post-treatment [52]. Furthermore, the long-term effects are promising, as research indicates a reduction in relapse rates and sustained symptom relief for up to one year following treatment [53]. The evidence suggests that VR-based ETE may provide long-lasting relief for Hwa-Byung, a condition characterized by persistent physical and emotional symptoms. Thus, VR can be positioned as a valuable complement to conventional therapeutic modalities.

This study proposes a novel approach to addressing deficits in emotion regulation, particularly in culturally bound syndromes like Hwa-Byung, by integrating virtual reality. Recognizing that symptom expression is influenced by cultural context, we designed our approach to observe participants’ symptoms through a cultural perspective, identify core emotions, and develop tailored therapeutic methods accordingly. The study’s objective is to compare the safety, effectiveness, and economic feasibility of ETE and VR-based ETE to explore their impact on the core and related symptoms of Hwa-Byung. Should the results prove meaningful, this research could contribute not only to improving public health and quality of life for patients suffering from Hwa-Byung, but also to the modernization and popularization of traditional Korean medicine through its integration with advanced digital platforms such as VR.

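### The stated aim is VR-based ETE versus conventional ETE, but the 80% power is calculated for one experimental group versus control, so the trial is not powered for its stated aim

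*Protocol article*

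**What the plan says.** The aim appears in three places, each time as a comparison of the two active arms:

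- Abstract: to "assess the efficacy of Virtual Reality-based Emotion-to-Emotion Therapy (VR-based ETE) compared to conventional ETE".
- Section 1: "This study aims to determine the safety, effectiveness, and cost effectiveness of virtual reality-based emotion-to-emotion therapy compared to traditional emotion-to-emotion therapy for Hwa-Byung".
- Section 3: the "objective is to compare the safety, effectiveness, and economic feasibility of ETE and VR-based ETE".

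Section 2.4.3 sets a two-sided 5% level and 80% power, with 1:1:1 allocation. The planning values are given for one pair of groups: "We expect the HB-M reduction in the control group and experimental group to be 2.52 and 6.84, respectively", with a pooled SD of 5.178. The formula printed next uses other values (difference 7.8 − 2.8, SD 6.9) and gives about 30 per group. With 25% dropout allowed for, 32 per group are to be enrolled, 96 in all.

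Section 2.11.1 analyses the change in HB-M from baseline to 8 weeks with an independent t-test between two groups. The trial has three arms, and the section does not say which two are meant. No non-inferiority or equivalence margin is given anywhere.

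**The concern.** A reader of the abstract expects the stated power to apply to VR-ETE versus ETE. It does not. Section 2.4.3 has one response for a single experimental group and one for control, and nothing separates the two experimental arms. Section 2.11.1 does not resolve this, because the pair to be tested is left open.

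The difference matters because the control group receives training materials only, whereas both active arms follow the same ETE protocol on the same 12-session schedule (section 2.5). The document gives no reason to expect the gap between the active arms to be as large as the gap between an active arm and control. If it is smaller, the comparison that the article puts first will probably be inconclusive, and nothing in the text prepares the reader for that.

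**Working it through.** **Inputs.** From section 2.4.3: two-sided α = 0.05, power 80%, 32 enrolled per arm, 25% dropout. Evaluable per arm: 32 × 0.75 = 24. The section holds two sets of planning values:

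- Text: difference 6.84 − 2.52 = 4.32, SD 5.178.
- Printed formula: difference 7.8 − 2.8 = 5.0, SD 6.9.

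**The plan's own figure.** n per group = 2 × SD² × (1.96 + 0.84)² / difference².

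- Formula values: 2 × 6.9² × 2.8² / 5.0² = 29.9, so 30. This reproduces the stated figure.
- Text values: 2 × 5.178² × 2.8² / 4.32² = 22.5, so 23 (24 with the t-test), not 30.
- Dropout: 30 / 0.75 = 40, not 32. The enrolled number follows only from the text values: 24 / 0.75 = 32.

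Both sets describe one contrast. Neither contains a VR-ETE minus ETE difference.

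**What the enrolled number gives.** Two-sample t-test with 24 per arm:

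- Standard error of a difference = SD × √(2/24): 1.495 (SD 5.178) or 1.992 (SD 6.9).
- Difference detectable with 80% power = 0.826 × SD.
- 95% CI half-width = 2.013 × standard error (t on 46 degrees of freedom).

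| 24 per arm | SD 5.178 (text) | SD 6.9 (formula) |
|---|---|---|
| Active vs control: power at the matching planned difference | 81% (4.32) | 69% (5.0) |
| VR-ETE vs ETE: difference detectable with 80% power | 4.28 | 5.70 |
| VR-ETE vs ETE: 95% CI half-width | 3.0 | 4.0 |
| VR-ETE vs ETE: power at 2.16 points | 29% | 19% |
| VR-ETE vs ETE: power at 1 point | 10% | 8% |

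The 2.16 points (half of 4.32) and the 1 point are assumptions, because the documents give no expected value for this contrast. The detectable difference and the interval width do not depend on them.

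The detectable difference compares with the planned active-versus-control effect as follows: 4.28 / 4.32 = 0.99 with the text values, and 5.70 / 5.0 = 1.14 with the formula values.

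**With no dropout** (32 per arm), the detectable difference is 3.68 or 4.91 points, and power at 2.16 points is 38% or 23%.

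**Size needed.** For 80% power at 2.16 points, about 92 evaluable per arm (SD 5.178) or 162 per arm (SD 6.9) would be required.

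**The case against.** *The trial can still address VR-ETE versus ETE.* This stands. Both arms are randomised concurrently and share the primary outcome, so the difference can be estimated with a confidence interval, and a very large difference would be detected. A reader might infer that the trial cannot answer its headline question. The documents support only that it is not powered for it.

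*Nobody claims equivalence.* This also stands. A reader might infer that the plan means to present a null result as VR being as good as ETE. The article says nothing of the kind: its language is of superiority and it sets no margin. The misreading is a foreseeable risk that one sentence would remove, but it is not an error in the text.

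*The aim is wider than VR versus ETE.* This stands in part. The discussion goes on to mention exploring the effect of both therapies on symptoms, and the introduction calls for further confirmation that ETE works, which the control arm serves. Even so, none of the three statements of aim mentions the control group.

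*The effect scenarios are arbitrary.* The documents give no minimally important HB-M difference, so it cannot be said that 2.16 points would be worthwhile. The scenario only illustrates. The conclusion rests on the detectable difference and the interval width.

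*The 80% itself is uncertain.* Correct. It holds for active versus control only under the values in the text; under those in the formula it is about 69%. A statement that 80% covers active versus control cannot be written until the two sets are reconciled.

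**Conclusion.** The point holds. The planned power refers to one active arm against control, while the stated aim is one active arm against the other. For the stated aim, 24 evaluable per arm give 80% power only for a difference of about 4.3 points (SD 5.178) to 5.7 points (SD 6.9). VR would have to add about as much to ETE as an active arm is assumed to add to training materials alone, or somewhat more. Power would be about 29% or 19% if the true difference were 2.16 points. The 95% CI half-width would be about 3.0 to 4.0 points.

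These figures assume the stated 25% dropout, a two-sided 5% t-test, no adjustment for multiplicity, and that the planning SD applies to both active arms. Which SD is right cannot be settled from the article, but the conclusion is the same under either and survives full retention. An analysis plan could name the contrasts, but it could not give the VR-ETE versus ETE comparison the power that the enrolled number lacks.

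**What to change.** 1. **Section 2.4.3.** First reconcile the two input sets (4.32 with SD 5.178; 5.0 with SD 6.9). Then state that the planned power refers to an active arm versus control only, and give its value for the reconciled inputs: at 24 per arm, about 81% under the text values or 69% under the formula values. Add the VR-ETE versus ETE difference detectable with 80% power (about 4.3 or 5.7 points).
2. **Section 2.11.1.** Replace the unnamed pair with the confirmatory contrasts, ETE versus control and VR-ETE versus control, with multiplicity control if both are confirmatory. Report VR-ETE minus ETE as an estimate with a 95% confidence interval, and say that a non-significant result is not evidence of equivalence.
3. **Abstract, section 1 and section 3.** Word the aim to match.

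This costs wording only and no extra participants. The downside is a more modest headline claim for VR. The alternative is to keep VR-ETE versus ETE as the primary aim and size the trial for it, with a justified difference or non-inferiority margin. At the illustrative 2.16 points that means about 92 to 162 evaluable per arm in place of 24, before allowing for dropout.

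### The sample-size paragraph mixes two incompatible sets of inputs, so its printed route from assumptions to 30 and then 32 per group does not reproduce

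*Protocol article*

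**What the plan says.** All of this is in section 2.4.3 (Sample Size) of the protocol article. The test is two-sided at 5%, with 80% power and 1:1:1 allocation. The expected effect is given first: "We expect the HB-M reduction in the control group and experimental group to be 2.52 and 6.84, respectively, and pooled standard deviation 5.178". The paragraph attributes these values to earlier work of similar design.

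The next sentence opens "Therefore, the required sample size for each group is expected to be" and prints 2 × 6.9² × (1.96 + 0.84)² / (7.8 − 2.8)², with a result of about 30 per group. The paragraph closes with the dropout allowance: "In addition, considering a dropout rate of 25%, we decided to register 32 participants per group, for a total of 96 participants".

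Section 2.11.1 (Primary Outcome) names an independent t-test between two groups on the change in HB-M. The abstract repeats the total of 96 but gives no derivation.

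**The concern.** The formula is presented as the consequence of the sentence before it, yet it uses none of that sentence's numbers. The values 6.9, 7.8 and 2.8 appear nowhere else in the article and have no stated source. The move from 30 to 32 is then described as an allowance for 25% dropout, which is far too small a step for that rate.

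The enrolment and power for the primary outcome both rest on this paragraph. As printed, a reader cannot derive 96, and cannot tell which effect and SD the 80% power refers to. That matters because the two sets of inputs give different power at the protocol's own dropout rate.

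**Working it through.** **Inputs (section 2.4.3)**
- Two-sided α = 0.05, power 0.80, equal groups, dropout 25%, enrolment 32 per group.
- Set A, the sentence: difference 6.84 − 2.52 = 4.32, SD 5.178, standardised effect 4.32/5.178 = 0.834.
- Set B, the formula: difference 7.8 − 2.8 = 5.0, SD 6.9, standardised effect 5.0/6.9 = 0.725.

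**1. Reproduce the printed 30.** With Set B, n = 2 × 6.9² × 2.8² / 5.0² = 29.86, so 30 per group. The printed result is correct for the formula's own inputs. The exponent on the denominator is flattened in the extracted text. The value 29.86 confirms that a square is meant, and this is not counted as an error.

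**2. Put the stated inputs into the same formula.** With Set A, n = 2 × 5.178² × 2.8² / 4.32² = 22.53, so 23 per group. The noncentral-t requirement for the two-sample t-test is 23.55, so 24 per group. Neither is 30.

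**3. Apply 25% dropout to the printed 30.** 30 / (1 − 0.25) = 40 per group. The cruder 30 × 1.25 gives 37.5, so 38. Neither is 32. The loss that 32 can absorb while leaving 30 is 1 − 30/32 = 6.25%.

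**4. Look for a route to 32.** With Set A and the t-test, 24 / 0.75 = 32 exactly. With Set A and the normal approximation, 23 / 0.75 = 30.7, so 31. With Set B, 25% dropout gives 40 (from 30), or 42 from the t-test requirement of 31. So 32 comes exactly from Set A with the t-test, and not from Set B.

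**5. Power for one pairwise two-sided 5% t-test (noncentral t).** With 32 enrolled and 25% lost, 32 × 0.75 = 24 per group remain.

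| Evaluable per group | Set A (4.32, SD 5.178) | Set B (5.0, SD 6.9) |
|---|---|---|
| 24 | 80.8% | 69.1% |
| 30 | 88.8% | 78.8% |
| 32 | 90.7% | 81.4% |

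By normal approximation, the figures at 24 per group are 82.4% for Set A and 70.9% for Set B.

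**The case against.** The strongest reply is that the design itself is sound and only the display is wrong. The sentence's inputs have a stated source and the formula's do not. The sourced inputs, under the t-test that section 2.11.1 names, need 24 per group, and 24/0.75 is exactly the 32 enrolled. On this reading the formula line is left over from another calculation, the 25% allowance was applied in full, and both 96 participants and 80% power stand.

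Most of this stands, and it rules out two stronger conclusions that a reader might draw. One is that the 25% dropout was ignored. The documents do not support that: 32 fails to follow from the printed 30, but it is fully consistent with a 25% allowance on the stated inputs. The other is that the trial is underpowered. That is not shown either, because the shortfall arises only on the unsourced inputs.

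The reply does not remove the inconsistency. The figure 24 is never printed, the only calculation shown uses other inputs, and nothing elsewhere in the article reconciles them. The benign reading is a good inference, but only the sponsor can confirm it.

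It could also be said that 69% treats every dropout as lost to the analysis, whereas sections 2.10 and 2.11.1 plan imputation in the full analysis set. The figure is indeed a complete-case one. However, section 2.2 schedules HB-M only at baseline, visit 12 and the follow-up visit, so imputation would have little to work from and the approximation is fair.

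**Conclusion.** Wrong as written. The paragraph combines two incompatible sets of inputs, and both links in its printed chain fail: the stated inputs give 23 or 24 per group rather than 30, and 30 at 25% dropout gives 40 rather than 32.

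The finding is that the derivation contradicts itself, not that power has been shown to be too low. On the sourced inputs, which are the better supported basis, 32 per group is right and power is 80.8% with 24 evaluable. If the formula's inputs are the real basis, power at the protocol's dropout rate is about 69%, some 11 points below the stated 80%. These figures assume a single pairwise comparison at an unadjusted two-sided 5% and complete-case analysis of 24 per group.

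**What to change.** Keep 96 participants and state in section 2.4.3 which inputs apply.

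- **If 2.52, 6.84 and 5.178 are the basis:** replace the formula and the figure of 30 with the two-sample t-test requirement (noncentral t) of 24 per group, followed by 24/0.75 = 32. The method must be named. The normal-approximation formula with these inputs gives 22.5, hence 23 and then 31 after dropout, so printing it would again fail to lead to 32.
- **If 6.9 and 5.0 are the basis:** give their source, correct the sentence before the formula, keep 32 per group, and restate power as about 69% at 25% dropout. Note that 80% by the printed formula would have needed 40 per group, 120 in total.

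The dropout rate should not be lowered to about 6% to make 30 and 32 agree, since the protocol offers no support for such a rate.

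The cost is one corrected paragraph and no extra participants. The downside is that, in the second case, the stated power becomes less favourable.
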